**Use of study data for future research**

Future research may help further the understanding of the studying and other related conditions, drug response and toxicity, and can help identify new drug targets or biomarkers that predict participant response to treatment. Therefore, de-identified data collected from this study will be stored and used for future research when consented by participants unless prohibited by local laws or REBs (in such case, consent for future use of collected de-identified study data will not be included in the local ICF).

For participants who consent to the use of their de-identified study data, data may be used after the study ends for future research related either to the drug, the mechanism of action, and the studying condition or its associated conditions.

## Safety and Other Assessments

The study's primary objective is to determine the safety and tolerability of the MediPharm Labs MPL-001 Oil, the investigational product in adolescents with chronic headache. To achieve this objective, treatment of emergent adverse events, vital signs, laboratory results, physical examinations, cannabis use disorder screening and concomitant therapy will be assessed. Study participants will be directed to record adverse events throughout the study. Self-reported information of adverse events from the patients will be reviewed with the study coordinator at each study visit.

## Adverse Events and Serious Adverse Events

### Definition of Adverse Events (AE)

Adverse event means any untoward medical occurrence in a clinical study where a participant administered a medicinal product, which does not necessarily have a causal association with the treatment. An AE can therefore be any unfavourable and/or unintended sign, symptom, or disease temporally associated with the use of a medicinal product, whether or not considered related to the medicinal product. AEs may also include pre-or post-treatment complications resulting from protocol-specified procedures, overdose, drug abuse/misuse reports, or occupational exposure. In addition, pre-existing events that increase in severity or frequency or change in nature during or as a consequence of participation in the clinical study will also be considered AEs.

### Definition of Serious Adverse Events (SAE)

An adverse event (AE) or suspected adverse reaction is considered "serious" if, in the view of either the investigator or sponsor, it results in any of the following outcomes: death, a life-threatening adverse event, inpatient hospitalization or prolongation of existing hospitalization, a persistent or significant disability/incapacity or substantial disruption of the ability to conduct normal life functions, or a congenital anomaly/birth defect.

Important medical events that may not result in death, be life-threatening or require hospitalization may be considered serious when, based upon appropriate medical judgment, they may jeopardize the participant and may require medical or surgical intervention to prevent one of the outcomes listed in this definition. Examples of such medical events include allergic bronchospasm requiring intensive treatment in an emergency room or at home, blood dyscrasias or convulsions that do not result in inpatient hospitalization, or drug dependency or drug abuse development.

### Classification of an Adverse Event

#### Severity of Event

The following guidelines will describe severity for adverse events (AEs) not included in the protocol defined grading system.

- **Mild** – Events require minimal or no treatment and do not interfere with the participant’s daily activities.
- **Moderate** – Events result in a low level of inconvenience or concern with the therapeutic measures. Moderate events may cause some interference with functioning.
- **Severe** – Events interrupt a participant's usual daily activity and require systemic drug therapy or other treatment. Severe events are usually potentially life-threatening or incapacitating. Of note, the term "severe" does not necessarily equate to "serious".

#### Relationship to Study INTERVENTION

All adverse events (AEs) must have their relationship to study intervention assessed by the clinician who examines and evaluates the participant based on temporal relationship and his/her clinical judgment. The degree of certainty about causality will be graded using the categories below. In a clinical trial, the study product must always be suspect.

- **Related** – There is clear evidence to suggest a causal relationship, and other possible contributing factors can be ruled out. The clinical event, including an abnormal laboratory test result, occurs in a plausible time relationship to study intervention administration and cannot be explained by concurrent disease or other drugs or chemicals. The response to the withdrawal of the study intervention (dechallenge) should be clinically plausible. The event must be pharmacologically or phenomenologically definitive, with use of a satisfactory rechallenge procedure if necessary.
- **Potentially Related** – There is some evidence to suggest a causal relationship (e.g., the event occurred within a reasonable time after administration of the trial medication). However, other factors may have contributed to the event (e.g., the participant’s clinical condition, other concomitant events). Although an AE may rate only as “possibly related” soon after discovery, it can be flagged as requiring more information and later be upgraded to “probably related” or “definitely related”, as appropriate.
- **Not Related** – The AE is completely independent of study intervention administration, and/or evidence exists that the event is definitely related to another etiology. There must be an alternative, definitive etiology documented by the clinician.
- **Unknown** – According to all the information available, there is not enough information for site investigator to make decision.

#### Expectedness

The site investigator at each study site will be responsible for determining whether an adverse event (AE) is expected or unexpected. An AE will be considered unexpected if the nature, severity, or frequency of the event is not consistent with the risk information previously described for the study intervention.

### Time Period and Frequency for Event Assessment and Follow-Up

The occurrence of an adverse event AE or SAE may come to the attention of study personnel during study visits and interviews of a study participant presenting for medical care or upon review by a study monitor.

All AEs, including local and systemic reactions not meeting SAEs' criteria, will be captured on the appropriate case report form (CRF) of REDCap. Information to be collected includes event description, time of onset, clinician's assessment of severity, relationship to study product (assessed only by those with the training and authority to make a diagnosis), and time of resolution/stabilization of the event. All AEs occurring while on the study must be documented appropriately regardless of relationship. All AEs will be followed to an adequate resolution.

Any medical condition present at the time that the participant is screened will be considered a baseline and not reported as an AE. However, if the study participant's condition deteriorates during the study, it will be recorded as an AE. Changes in the severity of an AE will be documented to allow an assessment of the duration of event at each level of severity to be performed. AEs characterized as intermittent require documentation of onset and duration of each episode.

The study team will record all reportable events with start dates occurring any time after informed consent is obtained and for the duration of study participation. At each study visit, the investigator will inquire about the occurrence of AE/SAEs since the last visit. Events will be followed for outcome information until resolution or stabilization.

### Adverse Event Reporting

All severe, life-threatening or fatal AEs that are definitely related to the intervention (defined in 9.3.3.2) from the time of informed consent signed to the end of visit 7 - must be entered in the CRFs within 24 hours of awareness and assessed by the site investigator.

All AEs from the time of informed consent signed to the end of visit 7 needs to be entered in the CRFs and assessed by the site investigator within 7 days of awareness. Participant self-reported AE (in daily eDiary) needs to be followed up and entered in REDCap (Research Electronic Data Capture) AE log, and assessed by site investigator.

### Serious Adverse Event Reporting

All Serious Adverse Events (SAE) must be reported in the REDCap database by the site investigator within 24 hours of becoming aware of the SAE. The initial report should contain as much information as available.

At a minimum, the report must contain:

- Name of Site and Qualified Investigator,

- Participant Identification Code,

- Adverse Event Term,

- Study Drug Dose and Start/Stop Dates

Fatal or life-threatening unexpected adverse drug reactions must be reported to Health Canada within 7 days after awareness. All other serious unexpected adverse drug reactions must be reported within 15 days after awareness.

### Reporting Events to Participants

If cannabis-related SAEs occur, study participants will be notified based on recommendations from the DSMB and Steering Committee to the Principal Investigator.

### Reporting of Pregnancy

Pregnancy tests (detection of human chorionic gonadotropin) will be completed using blood samples collected to investigate cannabinoid blood levels. At visit 1, a urine pregnancy test will be added on top of the blood pregnancy test to exclude patients with positive result from enrollment. Eligibility confirmation will still depend on the visit 1 blood pregnancy test result. Any participant who becomes pregnant will be offered to counsel and will be withdrawn from the study (investigational product use terminated).

# STATISTICAL CONSIDERATIONS

## Statistical Hypotheses

The primary endpoint (adverse events) will be analysed and presented descriptively with frequency counts and severity criteria. There are no pre specified statistical hypothesis.

## Sample Size Determination

The CAN-CHA trial is a tolerability study designed to identify a safe dose of a cannabis product in adolescents with chronic headache. Because of the within-participant study design, a sample size of 20 study participants should provide a reasonable characterization of the pattern of adverse event frequency and severity as dosage increases. To provide more generalizable data, we will recruit these 20 study participants across three chronic pain programs in Halifax, Vancouver, and Toronto.

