| Endpoints | **Primary Endpoint:**  The frequency and type of treatment-emergent adverse events among participants treated with CBD-enriched CHE reported daily and evaluated monthly before the subsequent dose escalation  **Secondary Endpoints:**   1. Number of headache-free days per month. 2. Percentage change in average daily pain intensity due to headache on the numeric rating scale (NRS) from baseline to each follow up visit. 3. Sleep, mood and function are to be reported using the percentage change in the scores of PROMIS (patient-reported outcome measurement information system) measures from the Pediatric Item Bank:    1. Pediatric Sleep-related Impairment – Short Form 8a    2. Pediatric Short Form v2.0 - Anxiety - 8a    3. Pediatric Short Form v2.0 - Depressive Symptoms 8a    4. Pediatric Pain Interference – Short Form 8a    5. Pediatric Positive Affect – Short Form 8a    6. Self-directed goal attainment will be reported as a percentage toward a physical, mental and social goal reported by participants at each monthly visit. 4. Family impact scores will be reported by PedsQL™ Family Impact Module, Version 2.0 and compared with baseline scores.   **Exploratory Endpoints:**   1. Steady-state plasma levels of bioactive cannabinoids, namely THC, CBD, 11-OH-THC, 7-OH-CBD, and Cannabichromene, during each follow up visit before dose escalation. 2. Genetic polymorphisms of genes encoding for CYP enzymes and the p-glycoprotein transporter and plasma levels of THC, CBD and their active metabolites in the study participants. |
| Number of Participants | 20 participants |
| Inclusion Criteria | Adolescent patients of the qualified investigator between the ages of 14-17 years with chronic headaches will be enrolled.  They must have headaches (migraine or tension-like features) on more than 15 days per month for more than 3 months and have failed at least two treatment options for either tolerability or efficacy.  Participants must be committed to using contraception, abstaining from recreational cannabis use, and working with psychology and physiotherapy teams as appropriate. |

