| Statistical Methodology | *Sample Size determination:*  Precedent suggests that a power calculation is not appropriate for a dose-finding study. The study site and the number of planned dose escalations are standard for clinical trials.  *Populations for Analyses:*  We will complete an intent to treat analysis. All participants who received the investigational product for at least one month will be included in the analysis to ensure that these data would be likely to represent the effects of the study intervention.  *Safety Analyses:*  The severity, frequency, and relationship of AEs to study intervention will be presented by System Organ Class (SOC). The start date, stop date, severity, relationship, expectedness, outcome, and duration of each AE will be reported. Serious treatment-emergent AEs will be presented either in a table or a listing.  *Baseline and Descriptive Statistics:*  We will perform the descriptive statistics to describe baseline characteristics and other outcomes. The proportions and frequencies will be used to categories the categorical variable. The mean, median, range or standard deviations will be used to categories the continuous endpoints. Subgroup summarization based on dose level or other criteria may also be conducted. Median concentrations of CBD, THC and the major metabolites will be reported with ranges for each sampling time point. The ratio of parent to metabolites will be reported to provide estimates of the variability in cannabinoid metabolism.  *Sub-Group Analyses:*  We will perform prespecified subgroup analysis of primary and secondary outcomes-based sex and dose. |

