# INTRODUCTION

## Study Rationale

Randomized Control Trials (RCTs) and open-label studies have demonstrated the well-defined margin of safety and efficacy of CBD and CBD-enriched CHE in children with intractable epilepsy.[[1-9](#_heading=h.184mhaj)] Chronic headaches are one of the most common pain syndromes in adolescence, and despite numerous treatment options, roughly only half of adolescents with Chronic Headache (C) experience remission. CBD and other cannabis products are being used off-label for the treatment of chronic headaches. [[10](#_heading=h.3jtnz0s)] Prescription cannabinoids (nabiximols) and other cannabis-based products containing THC are currently being used off-label in adolescents with chronic headaches. The overall purpose of this open-label phase 2 study is to generate clinical evidence on the safety, and tolerability of a CBD-enriched CHE in adolescents suffering from chronic headaches. Furthermore, the ideal tolerated dose derived from this study will inform a future RCT to explore the efficacy of CBD-enriched CHE in a larger cohort. In this study, participants will receive escalating doses to a maximum of 1.0mg/kg of CBD/day to treat the chronic headaches. There have been many historical challenges with studying cannabis products and cannabinoids due to difficulties in consistently obtaining products, variable quality control and stigma associated with cannabis. Canada has the opportunity to be a world leader in cannabis research. The successful outcomes from this research project have the potential to create a meaningful impact on the lives of Canadian adolescents, given the high prevalence of chronic headaches, severe morbidity, and the current lack of effective treatment options.

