# STUDY DESIGN

## Overall Design

This is multicenter phase 2, single group assignment, open-label dose-escalation, pharmacokinetic trial. A traditional 3+3 dose-finding design was not practical as all participants would not receive the lowest cannabinoid dose and the recommended “start low and go slow” approach to titration. The trial will be conducted across three centres in Canada and was designed in collaboration with youth from the KidsCAN Young Persons’ Advisory Group (YPAG) and the Solutions for Kids in Pain (SKIP) network. The Canadian Childhood Cannabinoid Clinical Trials Parent Advisory Committee provided insight on the outcome measurement tools and the consent form. Three youth advisors with chronic migraines have been involved throughout the study design process and will advise on recruitment strategies, reporting and dissemination as steering committee members. The youth engagement plan, findings and evaluation are described elsewhere (*publication under review)*. The research team held three virtual meetings with youth advisors to discuss which outcomes are important to youth, and decided on data collection methods and tools. The research team also co-designed the recruitment materials, including consent forms, with youth advisors. The PI will send safety reports annually to Health Canada as a Clinical Trial Notification to strengthen the evidence base of product specific cannabis data. The study will consist of three different phases: baseline (1 month), followed by escalating treatments monthly. Participants will wean in the same dosing increments over 4 weeks and will complete a pre and post study questionnaire.

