# STUDY INTERVENTION DISCONTINUATION AND PARTICIPANT DISCONTINUATION/WITHDRAWAL

## Dose limiting toxicity and Discontinuation of Study Intervention

Adverse events are categorized using the Common Terminology Criteria for Adverse Events (CTCAE version 5.0 dated 27 Nov 2017). If any of the following occur the participant will not move up to the next dose level (dose limiting toxicities):

1. Parental/youth report complaints of moderate mood elevation defined as exaggerated feelings of well-being which is disproportionate to the events and stimuli (Euphoria Grade 2)
2. Somnolence Grade 2 which includes moderate sedation (sleepiness and drowsiness) that limits instrumental activities of daily living
3. Cannabis-attributed diarrhea, Grade 2 or more defined as an increase of 4 - 6 stools per day over baseline; moderate increase in ostomy output compared to baseline; limiting instrumental activities of daily living
4. Unexplained tachycardia (w/out pain, fever, anemia etc.) requiring medical intervention
5. Unexplained hypotension requiring medical intervention
6. Non-infectious conjunctivitis Grade 2 defined as moderate decrease in visual acuity (best corrected visual acuity 20/40 and better or 3 lines or less decreased vision from known baseline) characterized by inflammation, swelling and redness to the conjunctiva of the eye.
7. Serious adverse events requiring hospitalization
8. Discretion of the participant, physician, or parents

Discontinuation from the study intervention does not mean interruption from the study, and remaining study procedures should be completed as indicated by the study protocol.

There will be no replacement of the study participants who were administered the investigational product, withdraw from the study, and lose follow-up (after signing an informed consent form). The main reason for the withdrawal of participants from the study will be noted in the participant's Case Record Form (CRF). The site investigator should contact the participants who fail to report during the follow-up visits which will be documented in the CRF.

Adverse events (AEs) and SAEs (Serious Adverse Events) will be reported according to Health Canada and Institutional regulations and reviewed by the data safety monitoring board (DSMB). The DSMB will hasten safety review if death is deemed related or potentially relevant to CBD-enriched CHE used in the study as the investigational product.

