### Baseline Descriptive Statistics

The primary statistical analysis will be a descriptive summary of the pattern of incidence and severity of adverse events across dosage levels. Conventional summary statistics will describe baseline characteristics and other outcomes (means, standard deviations, and medians, range and interquartile range (IQR) for numerical variables; counts and percentages for categorical variables). Summaries will be provided both overall and by dosage level. Medians, ranges and IQR, will be provided for the concentrations of CBD, THC and the primary metabolites at each sampling point. The ratio of parent compound concentration to metabolites will also be summarized to explore variability in cannabinoid metabolism. System organ class will present the severity, frequency, and relationship of treatment-emergent AEs to study intervention. The start date, stop date, severity, relationship, expectedness, outcome, and duration of each AE will be reported. Serious treatment-emergent AEs will be presented either in a table or a listing. The secondary outcomes, including pain, sleep impairment, depression, positive affect, anxiety and goal attainment scores, will be summarized at each timepoint; change from baseline will also be reported (both absolute and percentage change).

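### The protocol says the trial will identify a safe or ideal tolerated dose, but its primary endpoint and analysis only describe adverse events by dose and cannot name one

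*Protocol*

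**What the plan says.** **What the trial is for.** Section 10.2 (Sample Size Determination): "The CAN-CHA trial is a tolerability study designed to identify a safe dose of a cannabis product in adolescents with chronic headache". Study Rationale: "the ideal tolerated dose derived from this study will inform a future RCT to explore the efficacy of CBD-enriched CHE in a larger cohort". The Synopsis justifies the sample size in the same terms: "Precedent suggests that a power calculation is not appropriate for a dose-finding study". Overall Design says "A traditional 3+3 dose-finding design was not practical" and names no other rule for selecting a dose.

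**What is measured and analysed.** The primary endpoint is "The frequency and type of treatment-emergent adverse events among participants treated with CBD-enriched CHE reported daily and evaluated monthly", before each escalation. Section 10.1: "The primary endpoint (adverse events) will be analysed and presented descriptively with frequency counts and severity criteria"; the same section says that no hypothesis is pre-specified. Section 10.3.2: "The primary statistical analysis will be a descriptive summary of the pattern of incidence and severity of adverse events across dosage levels".

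**What marks a level as not tolerated.** Section 8.1 lists eight criteria under this rule: "If any of the following occur the participant will not move up to the next dose level (dose limiting toxicities". Seven are clinical events. The eighth is the discretion of the participant, physician or parents. Section 8.1 also says that participants who have received the product and then withdraw or are lost will not be replaced.

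**The concern.** The protocol promises a conclusion about dose, and the analysis it fixes does not lead to one. A table of adverse events by severity and dose level describes what happened. It does not say which level is safe or best tolerated, and no other section supplies that step.

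Section 8.1 contains the protocol's only working definition of a participant not tolerating a level. That status (criterion met, participant not moved up) appears in none of the primary, secondary or exploratory endpoints, nor in sections 10.3.1 to 10.3.3.

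The escalation rule also shapes the data. Only participants without a dose-limiting toxicity at one level go on to the next, and treated dropouts are not replaced. The group at the top level has therefore been filtered by tolerance of the lower ones. A low percentage of adverse events there can coexist with many of the 20 participants never having reached it. In an open-label study, the dose carried into the next trial could then rest on whichever summary is preferred once the results are known.

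**Working it through.** **Step 1: can the stated figure be reproduced?** The sample size of 20 comes with no target rate, precision, error rate or power, and the protocol says so openly. There is nothing to recompute, and this is not an arithmetic error.

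**Step 2: claim against analysis.**

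| Element | Where | Content |
|---|---|---|
| Conclusion claimed | 10.2, Study Rationale, Synopsis | A safe or ideal tolerated dose; a dose-finding study |
| Primary endpoint | Synopsis, Objectives and Endpoints | Frequency and type of adverse events |
| Primary analysis | 10.1, 10.3.2 | Descriptive, across dose levels |
| Marker of intolerance | 8.1 | Stops an individual's escalation; not analysed as such |
| Rule from data to dose | None | Conventional 3+3 set aside, nothing in its place |

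**Step 3: how selection affects the reading.** The protocol gives no toxicity rate, so the following counts are assumed: 1, 3, 3 and 2 participants with a dose-limiting toxicity at levels 1 to 4, and no other dropout. Let n be the number starting a level and x the number affected there. The next level starts with n − x. The per-level proportion is x/n; the cumulative proportion is the running total of x divided by 20.

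| Level | n | x | Per level | Cumulative |
|---|---|---|---|---|
| 1 | 20 | 1 | 1/20 = 5.0% | 1/20 = 5% |
| 2 | 20 − 1 = 19 | 3 | 3/19 = 15.8% | 4/20 = 20% |
| 3 | 19 − 3 = 16 | 3 | 3/16 = 18.8% | 7/20 = 35% |
| 4 | 16 − 3 = 13 | 2 | 2/13 = 15.4% | 9/20 = 45% |

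The top level looks slightly better tolerated than level 3 when read among those who reached it (15.4% against 18.8%), although 45% of the treated group has by then met a criterion. With a limit of one third, assumed only to show the effect, the per-level reading accepts all four levels and the cumulative reading stops at level 2. Exact 95% intervals are wide on either reading: 1.9% to 45.4% for 2/13 and 23.1% to 68.5% for 9/20.

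**Step 4: how often the two readings differ.** Inputs: 20 participants, four levels, the same toxicity probability p at each level among those starting it (assumed), affected participants not moving up, and the same assumed one-third limit. The expected cumulative proportion is 1 − (1 − p)^4. The last column comes from enumerating the binomial counts.

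| p per level | 1 − (1 − p)^4 | Readings name different levels |
|---|---|---|
| 2% | 1 − 0.98^4 = 7.8% | about 0% of trials |
| 5% | 1 − 0.95^4 = 18.5% | about 6% |
| 10% | 1 − 0.90^4 = 34.4% | about 55% |

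These figures hardly change with whether all lower levels must also pass (55% against 56% at p = 10%).

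**The case against.** **A descriptive analysis suits the study.** The primary objective is safety and tolerability. Section 10.2 goes on to say that 20 participants should give a reasonable picture of how adverse events change with dose, and a descriptive analysis without a hypothesis is ordinary for an open-label study of this size. All of that stands. No power calculation or hypothesis test is asked for; the difficulty is only the further claim to identify a dose.

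**The toxicity data are not lost.** A reader might infer that the dose-limiting toxicities go unanalysed altogether. The documents do not support that. The clinical events in section 8.1 are adverse events, so they fall within the primary endpoint, are summarised by severity and dose level, and will appear in the participant listings. What is not captured is the status of having been held from escalation, and the discretionary criterion need not produce an adverse event.

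**The analysis plan may add tables.** It may, and a missing table alone would not be a finding. But the dose claim, the primary endpoint and the primary analysis are all fixed in this protocol, and they do not connect.

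**The numbers rest on assumptions.** This is correct. The one-third limit is not the protocol's, and the 10% case sits close to it (34.4% against 33.3%), which raises disagreement. The Justification for Dose section expects good tolerability, describing the top dose as under 10% of that recommended in earlier paediatric studies. If toxicity is as rare as that implies, the readings agree.

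**Conclusion.** The mismatch is real. Sections 10.2, Study Rationale and the Synopsis claim a dose will be identified, while the endpoint and analysis fixed elsewhere describe adverse events and cannot identify one. Because escalation filters participants and treated dropouts are not replaced, by-dose percentages at the upper levels can understate intolerance, so this is more than loose wording.

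The practical size is conditional. It is negligible if dose-limiting toxicities are rare (about 0% disagreement at 2% per level), small at 5% (6%) and large at 10% (55%), all under an assumed one-third limit and constant rates. These figures are illustrative, not predictions. Larger figures can be obtained by adding a third reading based on an upper confidence limit, but they depend on a further rule about whether lower levels must also pass (about 78% against 64% at 10% per level, and 26% against 12% at 5%), so no weight is placed on them.

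A reader might also infer that the dose-limiting toxicity proportion ought to decide the dose against a set limit. The protocol does not support that: section 8.1 uses the criteria only to hold an individual's escalation, and one criterion is discretionary. The point is worth correcting before data are reviewed. It does not undermine the trial as a description of tolerability.

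**What to change.** Reconcile the sections in one of two ways.

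(a) Reword section 10.2, the Study Rationale and the Synopsis so that the trial describes adverse events and tolerability across the dose levels given, and remove the claim to identify a safe or ideal tolerated dose.

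(b) If the claim is kept, add a named tolerability measure to section 4 (Objectives and Endpoints) and section 10.3.2: the number and proportion of participants meeting a section 8.1 criterion at each level, with discretionary holds shown separately and exact confidence intervals. Report it both among those who started the level and cumulatively among all treated participants. The sponsor and the DSMB should then state, before data are reviewed, how this measure will inform the dose carried forward. No limit or dose is proposed here.

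Option (a) costs wording and a more modest claim. Option (b) costs one extra table from data already collected, plus an advance commitment on how it will be read.
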